# Driving pressure during general anesthesia for minimally invasive abdominal surgery (GENERATOR)—study protocol of a randomized clinical trial

**DOI:** 10.1186/s13063-024-08479-x

**Published:** 2024-10-26

**Keywords:** Mechanical ventilation, Intraoperative ventilation, Driving pressure, Positive end − expiratory pressure, Recruitment maneuver, Minimally invasive abdominal surgery, Pulmonary complications, Postoperative complications, Postoperative pulmonary complications

## Abstract

**Background:**

Intraoperative driving pressure (ΔP) has an independent association with the development of postoperative pulmonary complications (PPCs) in patients receiving ventilation during general anesthesia for major surgery. Ventilation with high intraoperative positive end–expiratory pressure (PEEP) with recruitment maneuvers (RMs) that result in a low ΔP has the potential to prevent PPCs. This trial tests the hypothesis that compared to standard low PEEP without RMs, an individualized high PEEP strategy, titrated to the lowest ΔP, with RMs prevents PPCs in patients receiving intraoperative protective ventilation during anesthesia for minimally invasive abdominal surgery.

**Methods:**

“DrivinG prEssure duriNg gEneRal AnesThesia fOr minimally invasive abdominal suRgery (GENERATOR)” is an international, multicenter, two–group, patient and outcome–assessor blinded randomized clinical trial. In total, 1806 adult patients scheduled for minimally invasive abdominal surgery and with an increased risk of PPCs based on (i) the ARISCAT risk score for PPCs (≥ 26 points) and/or (ii) a combination of age > 40 years and scheduled surgery lasting > 2 h and planned to receive an intra–arterial catheter for blood pressure monitoring during the surgery will be included. Patients are assigned to either an intraoperative ventilation strategy with individualized high PEEP, titrated to the lowest ΔP, with RMs or one with a standard low PEEP of 5 cm H_2_O without RMs. The primary outcome is a collapsed composite endpoint of PPCs until postoperative day 5.

**Discussion:**

GENERATOR will be the first adequately powered randomized clinical trial to compare the effects of individualized high PEEP with RMs versus standard low PEEP without RMs on the occurrence of PPCs after minimally invasive abdominal surgery. The results of the GENERATOR trial will support anesthesiologists in their decisions regarding PEEP settings during minimally invasive abdominal surgery.

**Trial registration:**

GENERATOR is registered at ClinicalTrials.gov (study identifier: NCT06101511) on 26 October 2023.

**Supplementary Information:**

The online version contains supplementary material available at 10.1186/s13063-024-08479-x.

## Background

Postoperative complications of up to 40% have been reported in patients receiving ventilation during general anesthesia for major surgery [1–4]. Postoperative complications that involve the lungs, so–called postoperative pulmonary complications (PPCs), greatly increase length of hospital stay and even mortality [3]. Considering an estimated 55 million abdominal surgery procedures are performed globally each year, even a slight reduction in PPCs would have a significant impact on healthcare costs [4, 5].

Intraoperative lung–protective ventilation may prevent PPCs [6, 7]. Intraoperative driving pressure (ΔP) has an independent association with PPCs [8]. ΔP is dependent on positive end–expiratory pressure (PEEP) and recruitment maneuvers (RMs): when PEEP with RMs increases aerated lung tissue, ΔP will remain low or can even decrease. However, when PEEP with RMs causes overdistention of lung tissue, ΔP will increase. Accordingly, ΔP has been proposed as a digital biomarker for guiding intraoperative PEEP settings [8]. Currently, a trial named “Driving prESsure DurIng GeNeral AnesThesIa fOr open abdomiNal surgery” (DESIGNATION) tests whether individualized high PEEP with RMs targeting a low ΔP compared to standard low PEEP without RMs reduces the incidence of PPCs in patients planned for open abdominal surgery [9].

Over the past decade, minimally invasive abdominal surgery has become more popular than open abdominal surgery. The rapidly expanding group of patients undergoing minimally invasive abdominal surgery represents a challenging cohort, as both the Trendelenburg positioning and the pneumoperitoneum cause a cephalad shift of the diaphragm, potentially changing the effects of PEEP with RMs on the amount of aerated lung tissue [10]. Consequently, this could have an effect on the incidence of PPCs in this population. A recent worldwide prospective observational study showed that 65% of patients undergoing minimally invasive abdominal surgery are at increased risk for developing PPCs, and the association between intraoperative ΔP and PPCs was found to be much stronger in patients undergoing minimally invasive abdominal surgery compared to those undergoing open abdominal surgery [11, 12]. It remains uncertain whether the ventilatory approach tested in DESIGNATION could also prevent PPCs in patients undergoing minimally invasive abdominal surgery. ΔP can be reliably and reproducibly determined during pneumoperitoneum [12]. In addition, ΔP and intra–abdominal pressure (IAP) have a linear relationship. When IAP increases, ΔP will increase too [13]. Higher PEEP settings have the potential to (partially) prevent this increase in ΔP [14].

This randomized clinical trial, named “DrivinG prEssure duriNg gEneRal AnesThesia fOr minimally invasive abdominal SurgeRy” (GENERATOR), assesses whether individualized high PEEP, titrated to the lowest ΔP, with RMs reduces PPCs in patients undergoing minimally invasive abdominal surgery.

## Methods

### Objectives and design

This investigator − initiated, international, multicenter, prospective, two–group, patient and outcome-assessor blinded randomized clinical trial (RCT) tests the hypothesis that in patients scheduled for minimally invasive abdominal surgery and at increased risk for PPCs, an individualized high PEEP strategy, titrated to the lowest ΔP, with RMs prevents PPCs when compared to a ventilation strategy that uses standard low PEEP without RMs. We further hypothesize that the individualized high PEEP strategy with RMs shortens duration of hospital stay and reduces the associated healthcare costs. A total of 1806 patients will be recruited in 20 academic and community hospitals in The Netherlands, Germany, Austria, Spain, and Italy (Table 4 in Appendix 1). Included patients will be randomly allocated in a 1:1 ratio to one of two intraoperative mechanical ventilation strategies (*see* Consolidated Standards of Reporting Trials (CONSORT) diagram in Fig. 1). The study design of GENERATOR is based on the ongoing DESIGNATION trial conducted by our group [9].

**Fig. 1 Fig1:**
[figure not shown]
Consolidated Standards of Reporting Trials (CONSORT) diagram for the “DrivinG prEssure duriNg gEneRal AnesThesia fOr minimally invasive abdominal suRgery (GENERATOR)” trial

### Trial population

In order to be eligible to participate in this trial, a patient must meet the following criteria:Age > 18 years; *AND*
Scheduled for minimally invasive abdominal surgery; *AND*
At increased (i.e., intermediate or high) risk of PPCs according to the “Assess Respiratory Risk in Surgical Patients in Catalonia” (ARISCAT) score (≥ 26 points, Table 1 [3]; *AND*/*OR* at increased risk of PPCs based on the combination of age > 40 years and scheduled surgery lasting > 2 h and planned to receive an intra–arterial catheter for blood pressure monitoring during the surgery [15]; *AND*
Signed written informed consent

**Table 1 Tab1:** Assess Respiratory Risk in Surgical Patients in Catalonia scores

Risk for PPCs of variables selected for the logistic regression model			
	**Multivariate analysis**	*Β* coefficients	Risk score
	**OR (95% CI)** *N* = 1625		
Age, years			
≤ 50	1		
51–80	1.4 (0.6–3.3)	0.331	3
> 80	5.1 (1.9–13.3)	1.619	16
Preoperative SpO_2_, %			
≥ 96	1		
91–95	2.2 (1.2–4.2)	0.802	8
≤ 90	10.7 (4.1–28.1)	2.375	24
Respiratory infection in the last month	5.5 (2.6–11.5)	1.698	17
Preoperative anemia (≤ 10 g/dL)	3.0 (1.4–6.5)	1.105	11
Surgical incision			
Peripheral	1		
Upper abdominal	4.4 (2.3–8.5)	1.480	15
Intrathoracic	11.4 (4.9–26.0)	2.431	24
Duration of surgery, h			
≤ 2	1		
> 2 to 3	4.9 (2.4–10.1)	1.593	16
> 3	9.7 (4.7–19.9)	2.268	23
Emergency procedure	2.2 (1.04–4.5)	0.768	8

*SpO*_*2*_, oxyhemoglobin saturation by pulse oximetry breathing air in supine position

High or intermediate risk for postoperative pulmonary complications following abdominal surgery: ARISCAT risk score ≥ 26

Patients are excluded if they are scheduled for open abdominal surgery, combined abdominal and intra − thoracic surgery, or surgery in the prone or lateral position. Patients with a confirmed pregnancy or patients who consented for another interventional trial during anesthesia are not eligible. Other exclusion criteria are having received mechanical ventilation for longer than 30 min within the last 5 days prior to the current surgery, patients who are expected to require postoperative ventilation in the intensive care unit (ICU) or post–anesthesia care unit, expected hemodynamic instability or intractable shock and severe cardiac disease (New York Heart Association class (NYHA) III or IV, acute coronary syndrome (ACS) or persistent ventricular tachyarrhythmias). In addition, patients with a history of acute respiratory distress syndrome (ARDS), any major previous lung surgery (e.g., lung resection) and severe chronic obstructive pulmonary disease (COPD) with (noninvasive) ventilation or oxygen therapy at home or repeated systemic corticosteroid therapy for acute exacerbations of COPD are excluded as well.

### Standard ventilation management

In both groups, patients are ventilated in volume–controlled mode at the lowest possible inspired oxygen fraction (FiO_2_), with a minimum of 0.4, to maintain peripheral oxygen saturation (SpO_2_) above 90%. A pause time, between inspiration and exhalation, of 15% for each breath will be used. Inspiratory to expiratory ratio (I:E) is set at 1:2, and the respiratory rate is adjusted to target normocapnia (end–tidal carbon dioxide partial pressure between 35 and 45 mmHg [4.6 and 5.9 kPa]). Tidal volume (*V*_*T*_) is set at 8 ml/kg predicted body weight (PBW), calculated using a predefined formula: 50 + 0.91 × (centimeters of height − 152.4) for males and 45.5 + 0.91 × (centimeters of height − 152.4) for females. Ventilation management and the intervention described below are similar to the ongoing DESIGNATION trial [9].

### Intervention

Patients randomized to the individualized high PEEP with RMs group will start with a PEEP of 10 cm H_2_O and will receive a RM followed by the decremental PEEP trial. RMs are conducted solely in a hemodynamically stable situation, as judged by the attending anesthesiologist. For this, the ventilator is kept in volume–controlled ventilation mode, with the respiratory rate set at 15 breaths per minute. In intervals of 15 s, PEEP is increased in steps of 5 cm H_2_O, starting at 10 cm H_2_O up to 20 cm H_2_O. The first RM will be conducted in the position in which the surgery will be performed, after abdominal insufflation and placement of all surgical instruments, i.e., in a steady state with sufficient working space for the surgeon. The surgeon is allowed to start surgery if no significant external pressure is applied on the abdomen and no new instruments are planned to be inserted. The RM will be repeated after any disconnection from the ventilator. The decremental PEEP trial is performed directly following the first RM, starting at a PEEP of 20 cm H_2_O with the respiratory rate set at 15 breaths per minute while the ventilator remains in volume–controlled ventilation mode. Every 20 s, PEEP is decreased in steps of 2 cm H_2_O until a minimum level of 6 cm H_2_O. Following each step, the resulting ΔP is calculated by subtracting PEEP from the plateau pressure (*P*
_plat_). Next, a ΔP–PEEP graph is drawn by plotting ΔP against PEEP, as shown in Fig. 2. The highest level of PEEP with the lowest ΔP is determined from the ΔP–PEEP graph. If no clear nadir is present and the driving pressure is fluctuating within a 2-cm H_2_O difference at maximum, 12 cm H_2_O PEEP will be selected. The decremental PEEP trial is followed by a second RM, after which the individualized PEEP will be set, as determined by the decremental PEEP trial and maintained until the end of ventilation (Fig. 3).

**Fig. 2 Fig2:**
[figure not shown]
Examples of the “ΔP–PEEP” graph. The arrow represents the optimal PEEP

**Fig. 3 Fig3:**
[figure not shown]
Overview of the intervention: the recruitment maneuvers and decremental PEEP trial. See text for a detailed description of the recruitment maneuvers and the decremental PEEP trial. The numbers projected in each bar represent the duration of each step in seconds

### Conversion to laparotomy

In case of conversion to laparotomy, the PEEP will be set to 10 cm H_2_O during the conversion. After opening of the abdomen, the decremental PEEP trial will be repeated and the correct PEEP will be set until the end of surgery or until another radical change in patient position or intra–abdominal pressure.

### Control group

Patients randomized to the standard low PEEP without RMs group will receive 5 cm H_2_O PEEP for the complete duration of intraoperative ventilation. This specific PEEP level of 5 cm H_2_O has been selected as it represents the most commonly selected PEEP level in daily clinical practice [1, 16]. They will neither undergo the planned RMs nor a decremental PEEP trial.

### Rescue strategies

Desaturation (defined as SpO_2_ ≤ 90% or if preoperative SpO_2_ < 90% an absolute decrease in SpO_2_ > 5%) in patients receiving the individualized high PEEP with RMs strategy could reflect the presence of overdistention of aerated lung tissue, despite a low ΔP. If desaturations occur and there are no airway problems, severe hemodynamic impairment or ventilator malfunction, a rescue strategy is allowed. This strategy involves a stepwise reduction in PEEP and eventually increase of FiO_2_ (Table 2). In the standard low PEEP group without RMs, desaturation may indicate the presence of atelectasis. If desaturations occurs and there are no airway problems, severe hemodynamic impairment or ventilator malfunction, a rescue strategy is allowed by increasing FiO_2_ first, eventually followed by RM and PEEP increases (Table 3).

**Table 2 Tab2:** Rescue for desaturation in the “individualized high PEEP with RMs” group

**Rescue for desaturation**		
**Step**	**PEEP**	**FiO**_**2**_
1	20	0.4
2	18	0.4
3	16	0.4
4	14	0.4
5	12	0.4
6	12	0.5
7	12	0.6
8	10	0.6
9	8	0.6
10	6	0.6
11	6	0.7
12	6	0.8

Down-titration of PEEP as rescue of desaturation. Starts at the level of PEEP set after the decremental PEEP trial

**Table 3 Tab3:** Rescue for desaturation in the “standard low PEEP without RMs” group

**Rescue for desaturation**		
**Step**	**PEEP**	**FiO**_**2**_
1	5	0.4
2	5	0.5
3	5	0.6
4	5	0.7
5	5	0.8
6	6	0.8
7	RM	

Up-titration of PEEP and recruitment maneuvers (RM) as rescue of desaturation

### Preapproved protocol deviations

In both groups, the attending anesthesiologist is allowed to change ventilator settings at any time point upon the surgeons’ request or if concerns about patient safety arise. If one of the following complications occurs and does not respond to conventional therapy, PEEP can be changed, according to the judgement of the anesthesiologist in charge:(i)After PEEP titration, a mean arterial pressure (MAP) < 65 mmHg, lasting > 1 min and not responding to fluids and/or vasoactive drugs [17];(ii)New arrhythmias not responding to the treatment suggested by the Advanced Cardiac Life Support (ACLS) guidelines [18];(iii)Need for a dosage of vasoactive drugs at the highest level tolerated, according to the decision of the anesthesiologist in charge;(iv)Need of massive transfusion, more than five units of blood to maintain hematocrit > 21% and hemoglobin > 7 mg/dL; and(v)Surgical complication resulting in life–threatening situation.

Any deviation from the protocol, excluding those mentioned above, are classified as protocol violations. Protocol violations are to be reported and will be discussed with the data safety monitoring board (DSMB).

### Standard procedures

Throughout the intraoperative period, routine elements of general anesthesia and surgery, including the intra-abdominal CO_2_ insufflation pressure and the use of neuromuscular blocking agents, are to be determined by the attending anesthesiologist and surgeon. Postoperative pain management, physiotherapeutic procedures, and fluid management will be administered according to each center’s specific expertise and routine clinical practice, ensuring minimal interference with the trial intervention. Quantitative neuromuscular monitoring, e.g., train-of-four (TOF) is required and residual curarization should be excluded prior to extubation (e.g., TOF > 0.9). It is strongly recommended to adhere to the Enhanced Recovery After Surgery (ERAS) guidelines.

### Minimization of bias

The local investigators perform randomization using the randomization tool in Castor Electronic Data Capture (EDC) [19]. Included patients will be randomly allocated in a 1:1 ratio to the individualized high PEEP with RMs group or the standard low PEEP group without RMs. The allocation sequence is generated by Castor EDC, uses permuted blocks with a maximum block size of 6, and is stratified per center and by body mass index (≤ 30 vs. > 30 kg/m^2^). Further minimization of bias will be achieved by involving at least two independent investigators per site. One investigator will be responsible for the preoperative and intraoperative trial period. A second investigator, who will remain blinded for treatment allocation, will score the primary and secondary postoperative outcome measures. Inherently to the type of intervention, the attending anesthesiologist is not blinded. Other caregivers, including the surgeon, research staff and ward nurses are blinded to treatment allocation.

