After induction of anesthesia, variables are collected hourly during the intraoperative period. These variables include ventilator settings, vital parameters, intra-abdominal pressure, administered fluids and vasoactive drugs, blood transfusions, need for rescue strategy for hypoxemia, intraoperative complications possibly related to PEEP titrations, preapproved protocol deviations and violations, details of anesthesia (type, epidural analgesia, neuromuscular function monitoring), patient positioning during surgery, arterial blood gas results (only if deemed necessary for clinical care for the patient), amount of fluid loss, and duration of both surgery and anesthesia procedures. Patients allocated to the individualized high PEEP with RMs group will have their plateau pressure recorded at the end of each decremental PEEP trial step and a ΔP–PEEP graph will be drawn.

Postoperatively, clinical data and the occurrence of pulmonary and extrapulmonary postoperative complications are collected. Blood tests and chest imaging will only be performed when considered necessary for the patients’ clinical care. Life status (death or alive) will be recorded during the first five postoperative days and at day 90 after surgery. Total length of stay in hospital, unplanned admission to an intensive care unit (ICU), and length of stay in the ICU are captured as well. To assess the health − related quality of life, the validated and commonly used EQ − 5D − 5L questionnaire will be sent out by email at day 90 after surgery to Dutch patients.

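### The protocol declares the surgeon and research staff blinded, but its own procedures contradict this, and the blinded assessor does not control which images and antibiotic courses exist to be scored

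*Protocol article*

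**What the plan says.** All references are to the protocol article.

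- **Minimization of bias.** One role is named as unblinded: "Inherently to the type of intervention, the attending anesthesiologist is not blinded". The next sentence covers everyone else: "Other caregivers, including the surgeon, research staff and ward nurses are blinded to treatment allocation". The same section has local investigators perform the randomisation. It makes one investigator responsible for the preoperative and intraoperative period, and a second, blinded investigator responsible for scoring postoperative outcomes.
- **Intervention.** The first recruitment maneuver takes place "after abdominal insufflation and placement of all surgical instruments, i.e., in a steady state with sufficient working space for the surgeon". During this period the surgeon works under a condition: "The surgeon is allowed to start surgery if no significant external pressure is applied on the abdomen", and no new instruments may be planned. In the titration that follows, "PEEP is decreased in steps of 2 cm H_2_O until a minimum level of 6 cm H_2_O".
- **Conversion to laparotomy.** The decremental trial is repeated once the abdomen is open.
- **Control group.** "They will neither undergo the planned RMs nor a decremental PEEP trial". No sham pause or matching restriction is described.
- **Trial visits and data collection.** "Blood tests and chest imaging will only be performed when considered necessary" for the patient's clinical care.
- **Trial endpoints.** One component is enough to make a patient an event. Chest imaging and antibiotics for pneumonia are listed among the secondary (cost-effectiveness) parameters.
- **Discussion.** The limitations paragraph mentions the anesthesiologist only.

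**The concern.** The blinding sentence claims a property that the procedures do not deliver. A surgeon who has to finish placing instruments, avoid pressing on the abdomen and hold back new instruments in one arm only has a clear cue to allocation. The investigator who covers the intraoperative period cannot be blinded to what is done then, and whoever randomises knows the result.

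This bears on the primary endpoint because several components come into being only when a clinician orders a film or starts antibiotics. If someone who knows the arm influences those decisions, the arms can differ in ascertainment without differing in lung injury. An assessor who is blinded to allocation cannot undo that.

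**Working it through.** **1. Blinding claim against procedure**

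| Role | Declared | What the procedures imply |
|---|---|---|
| Surgeon | Blinded | Subject to timing and conduct restrictions in the intervention arm only |
| Research staff | Blinded | Some randomise; one covers the intraoperative period; plateau pressures are recorded and a ΔP–PEEP graph drawn in one arm only |
| Outcome assessor | Blinded | Separate person; nothing contradicts this |
| Patient, ward nurses | Blinded | Nothing contradicts this, provided allocation is not passed on |

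**2. Length of the one-arm procedure**, from the steps in the Intervention section

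- First recruitment maneuver: levels 10, 15, 20, so 3 × 15 s = 45 s.
- Decremental trial: 20 down to 6 in steps of 2, so (20 − 6)/2 + 1 = 8 levels × 20 s = 160 s.
- Second recruitment maneuver, assumed to follow the same steps: 45 s.
- Total: 45 + 160 + 45 = 250 s.

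This assumes that each level is held for its full interval. Counting seven decrements instead of eight levels gives 230 s.

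**3. Components that depend on a decision to image or treat**

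- A chest radiograph is named in the definitions of pulmonary infiltrate (v), atelectasis (vii), pleural effusion (ix), cardiopulmonary edema (x) and pneumothorax (xi): 5.
- Receipt of antibiotics is required for suspected pulmonary infection (iv): 1.
- Total: at least 6 of 11.
- ARDS (viii) is defined only by citation, so it is not counted.
- Components (i), (ii), (iii) and (vi) name neither as a requirement.

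**4. How sensitive the comparison is to ascertainment**

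The plan's own figure comes first, with p1 = 0.30, p2 = 0.24, two-sided alpha 0.05, power 80%, 1:1 allocation and p̄ = 0.27:

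n = [1.960 √(2 × 0.27 × 0.73) + 0.842 √(0.30 × 0.70 + 0.24 × 0.76)]² / 0.06² = 859 per arm.

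The stated 860 is reproduced; power at 860 is 80.1%.

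The documents give no size for any ascertainment difference d, so d = 1, 2 and 3 percentage points are assumptions. With SE0 = √(2p̄(1 − p̄)/n), SE1 = √((p1q1 + p2q2)/n), q = 1 − p and n = 860:

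P(reject) = Φ((d − 1.96 SE0)/SE1) + Φ((−d − 1.96 SE0)/SE1).

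For d = 0.02 with no true effect (0.30 observed against 0.28), SE0 and SE1 are both about 0.0219, and P(reject) = 0.148 + 0.002 = 0.150.

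| Assumed d | False-positive rate, no true effect | Power for 30% vs 24%, bias towards null | Power, bias away from null |
|---|---|---|---|
| 0 | 5% | 80% | 80% |
| 1 point | 7.4% | 64% | 91% |
| 2 points | 15.0% | 46% | 97% |
| 3 points | 28.1% | 28% | 99% |

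These rows show scale. They do not estimate what will happen in this trial.

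**The case against.** **The headline label does not include the surgeon.** The abstract, the design section and the conclusion call the trial patient and outcome-assessor blinded, and the Discussion claims full blinding only for patients and postoperative assessors. This stands. A reader might infer that the trial's advertised blinding is false; the documents do not support that. The fault lies in one sentence on the other caregivers and in a limitations paragraph that repeats its gap.

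**Unblinding of the surgeon is inferred.** The Intervention text is permissive and does not say that the surgeon is told what is running. A condensed article may omit a site procedure that hides it. This also stands, so the supportable wording is that the surgeon can readily infer the arm, not that the surgeon will know it. Two other features do not restore blinding. A recruitment maneuver is the last rescue step for controls, but it is not the planned titration. In both arms "the attending anesthesiologist is allowed to change ventilator settings at any time point upon the surgeons’ request", which if anything gives the surgeon a further reason to discuss settings.

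**The roles are clear in context.** The section does separate the intraoperative investigator from the blinded assessor. That protects scoring, but the unqualified term for research staff is still wrong as written.

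**The path to bias is incomplete in the text.** No section says who orders postoperative imaging or antibiotics. Bias needs someone who knows the arm, who influences ordering, and who does so differently by arm. Only the first step has textual support. A reader might attach a single figure: 5 points more imaging in one arm with 30% of the extra films positive gives 0.05 × 0.30 = 1.5 points, a quarter of the planned 6. Those inputs have no source, and 1.5 is their upper end: it falls to 0 if every such patient is already an event through another component.

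**Part of the remedy exists.** Imaging and antibiotic use are already secondary parameters, and the Discussion promises each complication separately. This stands; what is missing is their stated use as a check on ascertainment. The sensitivity analysis could sit in the statistical analysis plan, which is not shown, so its absence here is not itself a fault.

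**Conclusion.** The statement that the surgeon and research staff are blinded is wrong as written: the Intervention, Control group and Minimization of bias sections contradict it. The limitations paragraph is correspondingly incomplete. The consequence for the primary endpoint is a risk and has not been shown to occur. At least 6 of 11 components depend on a decision to image or to give antibiotics, and blinded scoring does not control which of those decisions are made.

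A reader might go further and conclude that the surgeon's knowledge will bias the result, or bias it towards the intervention. The documents do not support either: they do not say who orders, and neither direction nor size can be derived. What can be said is that small differences would matter at this sample size, under the assumed 1 to 3 points. The matter is worth correcting because the correction is cheap and leaves treatment, sample size and primary analysis unchanged.

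**What to change.** 1. In Minimization of bias and in the limitations paragraph, list the surgeon, theatre staff and the randomising or intraoperative investigator as not (reliably) blinded. List patients, ward nurses and the postoperative assessor as blinded. Alternatively, describe how the surgeon is kept unaware of allocation.
2. Require that anyone who knows the allocation does not pass it to the ward or to the outcome assessor.
3. State that the by-arm comparison of chest imaging and antibiotic use, already among the secondary parameters, also serves as a check for differential ascertainment of the primary endpoint.
4. Add a sensitivity analysis of the composite restricted to components whose definitions require neither ordered imaging nor antibiotics: (i), (ii), (iii) and (vi). Present it as a robustness check and not as a bias-free endpoint, because oxygen, ventilation and bronchodilator use also involve clinical discretion.

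The cost is a slightly less favourable blinding statement, an instruction to sites, and one extra analysis of data already collected.
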